## Sample size

We estimate finasteride will reduce AS cessation rates by 50% (from 20% to 10%) after an average of 4 years follow-up. The sample size of 550 men (275 perm arm) is based on a time to event analysis with 90% power to reject H0: HR≠1, that is, the detection of a significant difference in AS cessation rates between arms by use of a two-sided log-rank test with alpha=0.05. We assume that 50% of control participants will progress (or be treated) during follow-up and that the HR is 0.65. The exact number needed is 271 per arm. We believe we will need to screen 1500 men to obtain 550 eligible, consenting recruits.

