Between 50% and 70% of men starting AS will receive either radical or palliative treatment over the following 10 years.^12^,^14^ In most men, radical treatment is initiated due to either a rising PSA or changes in Gleason grade on biopsy. Both are surrogate measures for disease progression. Many men are reluctant to undergo multiple biopsies and so most AS programmes are heavily reliant on PSA kinetics. For example, 25% of men in the Gothenberg screening trial^14^ and 43% of men in the Toronto trial who started AS received radical treatment due to a rising PSA alone.^4^ PSA values reflect benign enlargement and inflammation within the prostate^13^ as well as cancer growth. Therefore, many men with rising PSA values may not have disease progression and may not need radical treatment. For example, 65% of men within the PRIAS study^13^ and 72% in a large US series^15^ had favourable histology at radical prostatectomy after a period of AS. Within the ProtecT RCT, 50% of men randomised to monitoring received radical treatment with a <2% mortality rate at 10 years,^12^ highlighting the potential for overtreatment.

Various approaches have been tried to improve compliance with AS, including pharmacological interventions. The REDEEM study group randomised 302 men with low-risk PCa to 0.5 mg daily Dutasteride or placebo.^16^ At 3 years, the Dutasteride group had 10% fewer men with disease progression (defined as increasing cancer burden on biopsy or undergoing radical treatment). The ENACT study group randomised 227 men with low or intermediate-risk PCa to AS with or without 160 mg daily Enzalutamide.^17^ The addition of Enzalutamide reduced progression (pathological or therapeutic) by 46% at 12 months, although no difference was present at 2 years, there were side effects with this agent and its cost poses financial challenges to healthcare providers (especially if for long term AS regimens).

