## Statistical methods

### Participant population

The main endpoint analysis of progression from AS will be performed on all participants who have been randomised on an intention-to-treat basis. For the log-rank and Cox proportional hazards assessment of time to AS progression, the assumption of proportional hazards between the AS and control arms will be conducted by plotting log cumulative hazard plots. Kaplan-Meier plots will be produced to both aid the comparison of time to AS between treatment arms and to assess violation of the non-proportional hazard assumption. A formal assessment of proportional hazards will be performed by cumulative martingale residual plots with p value assessment of the Brownian bridge property present when proportional hazards is approximately satisfied. In the event of the occurrence of a significant degree of non-proportional hazards, then we will compare groups using Schemper’s weighted model. The analysis of Quality of Life (QOL) questionnaires will be performed on the set of men who complete the questionnaires. Tolerability of finasteride analysis will be performed on all participants randomised to finasteride.

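### The sample-size paragraph gives two incompatible sets of assumptions for the same AS-cessation comparison: 20% falling to 10% (HR about 0.47), and a 50% control rate with HR 0.65

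*Protocol article*

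**What the plan says.** All the planning figures stand in one paragraph, the Sample size section of the protocol article.

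- Expected effect: "We estimate finasteride will reduce AS cessation rates by 50% (from 20% to 10%) after an average of 4 years follow-up".
- Basis of the calculation: "We assume that 50% of control participants will progress (or be treated) during follow-up and that the HR is 0.65".
- Test and power: the calculation is "based on a time to event analysis with 90% power to reject H0: HR≠1", "by use of a two-sided log-rank test with alpha=0.05", and is described as detecting a difference between arms in AS cessation rates.
- Result: "The exact number needed is 271 per arm", rounded up to 275 per arm, 550 in all.

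Table 1 makes the primary outcome adherence to AS. Its events are treatment for prostate cancer, death from prostate cancer, and leaving AS for any other reason. Progression is a separate secondary outcome in Box 1. The Participant population section nevertheless speaks of "The main endpoint analysis of progression from AS". No section connects the 20% and 10% figures with the 50% and HR 0.65.

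**The concern.** Both sets are attached to one log-rank comparison over one follow-up period (3 to 5 years, 4 on average), but they differ in both quantities that matter. The control event proportion is 20% or 50%, and the HR is about 0.47 or 0.65. Neither set can be derived from the other.

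The power of a log-rank test depends on the number of events and the HR, and the two sets imply event counts that differ almost threefold. A reader cannot tell whether the trial expects about 82 events or about 237, or whether its target effect is a halving or a reduction of about a third in the hazard. This matters during the trial, because an observed cessation rate cannot be judged as on or off plan. It matters at reporting, because the effect for which the trial had 90% power is not settled. The conflict is easy to miss, since both sets lead to nearly the same sample size.

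**Working it through.** **Inputs from the protocol article.** Two-sided alpha 0.05, 90% power, log-rank test, 271 per arm calculated and 275 planned (Sample size); 1:1 allocation (Design). Set A: 20% control, 10% finasteride. Set B: 50% control, HR 0.65.

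**Assumptions of this check.** Proportional hazards, and no loss to follow-up (the article calls dropout low and gives no figure).

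**Formulas.** Finasteride event proportion pT = 1 − (1 − pC)^HR. Events with n per arm = n × (pC + pT). Required events:

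- Freedman: (1.960 + 1.282)² × ((1 + HR)/(1 − HR))²
- Schoenfeld: 4 × (1.960 + 1.282)² / (ln HR)²

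Power is Φ(√events × (1 − HR)/(1 + HR) − 1.960) by Freedman, and Φ(√events × |ln HR|/2 − 1.960) by Schoenfeld.

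**Step 1: reproduce the stated figure (set B).** pT = 1 − 0.5^0.65 = 0.363. Freedman events = 10.507 × (1.65/0.35)² = 233.5. Per arm: 233.5/(0.500 + 0.363) = 270.7, which rounds up to the stated 271. Schoenfeld gives about 227 events and 263 per arm.

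**Step 2: what set A implies.** HR = ln(0.90)/ln(0.80) = 0.472. If the halving is read as a halving of the hazard, HR = 0.50. Neither is 0.65. Conversely, HR 0.65 on a 20% control rate gives 1 − 0.8^0.65 = 13.5%, not 10%. Freedman events for HR 0.472 = 81.7, and 81.7/0.30 = 272.5 per arm, almost the same sample size as set B. Schoenfeld gives about 249-250 per arm.

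**Step 3: power with 275 per arm.**

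| Control rate | HR | Finasteride rate | Events | Power, Schoenfeld | Power, Freedman |
|---|---|---|---|---|---|
| 50% (set B) | 0.65 | 36.3% | 275 × 0.863 = 237 | 91.3% | 90.4% |
| 20% (set A) | 0.472 | 10.0% | 275 × 0.300 = 82.5 | 92.6% | 90.3% |
| 20% (sensitivity) | 0.65 | 13.5% | 275 × 0.335 = 92 | 54.3% | 53.0% |

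The third row takes its control rate from set A and its HR from set B. The article does not state that pairing.

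**Step 4: detectable effect at a 20% control rate.** Solving the power formulas for 90% with 275 per arm gives HR 0.49 (Schoenfeld) or 0.47 (Freedman). For 90% power at HR 0.65 with a 20% control rate, about 678 (Schoenfeld) to 699 (Freedman) men per arm would be needed.

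**The case against.** The best defence is that nothing has been miscalculated. The 271 follows from 50% and HR 0.65, and the planned 550 men also give about 90% power or more for 20% falling to 10%. This stands. A reader might infer from the 53-54% figure that the trial is underpowered; the documents do not support that. The figure arises only if cessation is near 20% and the effect is no stronger than HR 0.65, and the article never pairs those two values.

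A second defence is that the 50% describes a wider event, progression or treatment, so the two rates need not agree. The opposite inference, that the calculation was certainly made for the wrong endpoint, is also tempting. Neither can be established. The Participant population section itself calls the main endpoint progression from AS, so the wording in the Sample size section may be a loose term for leaving AS. On that reading the 20% and 50% conflict directly. On the wider reading, the 50% cannot supply the event count for a test of AS cessation, which is what the paragraph says is being tested. The inconsistency remains either way.

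A third temptation is to use the Introduction to decide between the rates: 50% to 70% of men starting AS "will receive either radical or palliative treatment over the following 10 years". Converting that to 4 years needs a constant hazard, which the article does not state, and those events are narrower than the Table 1 definition. It is not relied on here.

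Finally, the misstated null hypothesis is a slip of notation and does not affect the two-sided test.

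**Conclusion.** The point holds as an internal inconsistency in the assumptions, not as an arithmetic error. Control rates of 20% and 50%, and HRs of about 0.47 and 0.65, cannot both describe AS cessation over the same follow-up. The expected event count is therefore either about 82 or about 237.

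Taken whole, each set gives about 90-93% power with 275 per arm, so adequate power for a true halving is not in doubt on the plan's own figures. The exposure is conditional: should control cessation be 20% and the true HR 0.65, power would be 53-54%. These results assume proportional hazards and no loss to follow-up. The inconsistency itself also remains if the halving is read as HR 0.50.

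**What to change.** Keep 550 men. State a single control rate and a single HR for AS cessation as Table 1 defines it, with the expected number of events, and remove the other set or explain how it relates.

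- If 20% is the expected control cessation rate: give about 82 events, and say that 90% power applies only to an HR of about 0.47-0.49 or lower.
- If 50% with HR 0.65 is kept: say that the 50% refers to AS cessation, give about 237 events, and report power at a 20% cessation rate (53-54% for HR 0.65) as a labelled sensitivity figure.

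As a minor edit, write the null hypothesis as HR = 1.

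The cost is a revised paragraph and a less favourable conditional power statement. It needs no extra participants and no change to the primary test, the significance level or the analysis population.

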## Statistical methods

### Participant population

The main endpoint analysis of progression from AS will be performed on all participants who have been randomised on an intention-to-treat basis. For the log-rank and Cox proportional hazards assessment of time to AS progression, the assumption of proportional hazards between the AS and control arms will be conducted by plotting log cumulative hazard plots. Kaplan-Meier plots will be produced to both aid the comparison of time to AS between treatment arms and to assess violation of the non-proportional hazard assumption. A formal assessment of proportional hazards will be performed by cumulative martingale residual plots with p value assessment of the Brownian bridge property present when proportional hazards is approximately satisfied. In the event of the occurrence of a significant degree of non-proportional hazards, then we will compare groups using Schemper’s weighted model. The analysis of Quality of Life (QOL) questionnaires will be performed on the set of men who complete the questionnaires. Tolerability of finasteride analysis will be performed on all participants randomised to finasteride.

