**Methods and analysis:**

Finasteride in Active Surveillance for men with low and intermediate-risk prostate cancer (FINESSE) is a prospective, open-label, two-arm, phase 3 trial, in which men with low or intermediate PCa are randomised (1:1) to receive AS with or without finasteride (5 mg once a day for 2 years). Randomisation is stratified by age and PCa risk. AS includes regular prostate-specific antigen testing, MRI scans and the offer of repeat biopsy (at 3 years, or if imaging suggests progression). Additional MRI scans and/or biopsies will be performed for biochemical or clinical indications. We aim to recruit 550 men (aged 50 to 75 years) from up to eight sites. Active outpatient follow-up will be for 3–5 years (depending on date recruited), followed by passive registry-based follow-up for up to 10 years. Primary outcome is adherence to AS. Secondary outcomes include rates and type of disease progression, treatments received (for PCa and benign prostatic enlargement), overall and PCa-specific mortality, an understanding of patients/professionals views of this approach and health-related quality of life. An external panel of experts blinded to allocation will review all AS cessation and progression events. Trial pathologist’s and radiologist’s, blinded to allocation, will review representative cases. Analysis is Intention to Treat.

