### Randomisation and population

Randomisation is through a web-based tool bespoke to the King’s Clinical Trials Unit. Once participants have completed a signed consent form (online supplemental file 1), for example, Finesse Consent form, V.5.0 from 27 March 2024, their data will be stored on the system. The randomisation process is at the individual level using the method of permuted block randomisation with block sizes stratified by PCa risk (low vs intermediate) and participant age (<65 vs >65 years).

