### Eligibility criteria

Male subjects aged 50–75 years, with an estimated life expectancy of 10 years or more, who have opted for AS as their preferred PCa management option.Willing and able to provide written informed consent, or if appropriate, have an acceptable individual capable of giving consent on their behalf.Fit enough and suitable for radical treatment.Eastern Oncology Performance status ≤1.A histological diagnosis of Gleason grade group ≤2 (ie, Gleason grade 3+3=6 or 3+4=7) PCa within the last 6 months.Radiological stage ≤T2 b cN0 cM0 as defined by mpMRI imaging within the last 6 months (from the date of the mpMRI scan to the date of the patient’s randomisation). A copy of the mpMRI scan and report-confirming eligibility will be required.PSA ≤20 ng/mL. The result must be within 3 months of the date of the patient’s randomisation.PSA density ≤0.2 ng/mL/mL. The result must be within 3 months of the date of the patient’s randomisation.Biopsy criteria (via either transrectal or transperineal routes) within the last 6 months of the patient’s randomisation date):If targeted biopsy, then the maximum cancer core length is ≤10 mmIf targeted and systematic sampling biopsy, then the maximum cancer core length should be ≤10 mm, and ≤2 or ≤15% of non-targeted cores involved with cancer.If non-targeted biopsy (ie, USS template or sampling irrespective of lesions), then maximum cancer core length is ≤10 mm AND ≤3 or ≤20% of total number of cores involved with cancer.

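### The primary log-rank and Cox analysis, as described, does not mention the two factors that stratify randomisation; stratifying by them is a nearly free improvement, and the age boundary needs a small correction

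*Protocol article*

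**What the plan says.** The abstract states "Randomisation is stratified by age and PCa risk". The section Randomisation and population gives the detail: permuted blocks, "stratified by PCa risk (low vs intermediate) and participant age (<65 vs >65 years"). That makes four strata.

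The Sample size section is "based on a time to event analysis with 90% power", with the difference to be detected "by use of a two-sided log-rank test with alpha=0.05". Its planning values are: "We assume that 50% of control participants will progress (or be treated) during follow-up and that the HR is 0.65".

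Under Statistical methods, Participant population, the primary comparison is by intention to treat and is introduced with "For the log-rank and Cox proportional hazards assessment of time to AS progression". The text goes on to the proportional hazards checks (log cumulative hazard plots, Kaplan-Meier plots, cumulative martingale residuals) and to Schemper's weighted model as the fallback. It names no strata or covariates, and it does not say that the analysis is unstratified or unadjusted. Other statistical considerations refers to a statistical analysis plan, which is not at hand.

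Eligibility covers "Male subjects aged 50–75 years", so a man aged 65 can enter the trial.

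**The concern.** Stratified randomisation makes the arms more alike on risk and age than simple randomisation would. An unstratified log-rank test does not credit that balance: its variance is too large when the factors are prognostic, so the test is conservative. Leaving a prognostic factor out of a Cox model also pulls the estimated HR towards 1.

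The article gives some reason to expect risk group to matter. The Introduction says that the intermediate-risk population contains more lethal cancers than low-risk cohorts do. At stake is some power and precision on the primary question, although both factors are known for every man at randomisation. The calculated 271 per arm against 275 planned leaves a margin of only 8 men in total.

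The age cut-point matters here because an analysis by strata needs every man to belong to one.

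**Working it through.** **1. The plan's own figure.** Inputs from Sample size: HR 0.65, control event proportion 0.50, two-sided alpha 0.05, power 90%.

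- Events (Freedman): (1.960 + 1.282)² × [(1 + 0.65)/(1 − 0.65)]² = 10.51 × 22.22, giving 234.
- Finasteride event proportion: 1 − 0.5^0.65 = 0.363. Mean over arms: (0.500 + 0.363)/2 = 0.431.
- Men per arm: 234/0.4314/2 = 271.2, against 271 stated. The figure is reproduced. It is a calculation for a log-rank test without strata. (Schoenfeld gives 227 events and 264 per arm.)

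**2. What stratifying would change.** The documents give neither the strength nor the mix of the strata, so both are assumed. The set-ups share 550 men allocated 1:1, exponential times, follow-up uniform over 3 to 5 years, within-stratum HR 0.65 and 50% control events.

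- Set-up A: four equal strata, 4,000 trials per scenario.
- Set-up B: 60% intermediate risk, 50% in the older stratum, permuted blocks of 4, 3,000 trials per scenario.

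The Monte Carlo standard error of each power is about 0.5 points.

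| Set-up | Assumed HR for risk; age | Power unstratified | Power stratified | Gain (points) | Mean HR unstratified / stratified |
|---|---|---|---|---|---|
| A | none | 90.3% | 90.5% | 0.2 | – |
| B | 1; 1 | 90.1% | 89.8% | −0.3 | 0.651 / 0.651 |
| B | 1.5; 1 | 91.4% | 91.4% | 0.0 | 0.652 / 0.650 |
| B | 2; 0.8 | 90.8% | 91.8% | 1.0 | 0.656 / 0.648 |
| A | 2; 1 | 90.2% | 91.6% | 1.4 | – |
| A | 2.5; 1.5 | 87.1% | 90.3% | 3.2 | – |
| B | 3; 0.67 | 87.8% | 91.4% | 3.6 | 0.672 / 0.652 |
| A | 3; 1 | 86.5% | 91.4% | 4.9 | – |

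**3. Type I error** (set-up B, HR 1, standard error about 0.4 points; the four B scenarios in the order of the table). Unstratified: 5.5%, 4.7%, 4.3%, 3.6%. Stratified: 5.5%, 4.7%, 4.7%, 5.4%. The unstratified test becomes conservative as the strata become prognostic; it is not inflated.

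**4. The lower event rate.** Sample size also says "We estimate finasteride will reduce AS cessation rates by 50% (from 20% to 10%) after an average of 4 years follow-up". With 20% control events and HR 0.65, set-up B gives 52.5% against 53.1% (risk 2, age 0.8) and 51.5% against 53.3% (risk 3, age 0.67). The gain is at most about 2 points. The low power there comes from the event rate, not from the handling of strata, and the two planning rates are a separate matter.

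**5. The age boundary.** Under 65 and over 65 together omit 65. If ages in whole years were evenly spread over the 26 values from 50 to 75 (an assumption), 550/26 ≈ 21 men would be 65. If the system computes exact age from date of birth, almost none would fall in the gap.

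**The case against.** A reader might infer that the plan has chosen to ignore the stratification factors. The documents do not support that. The words unstratified and unadjusted do not appear, sizing a trial on a simple log-rank test does not bar a stratified analysis, and a journal article commonly leaves strata and covariates to the full protocol or the SAP. Silence cannot be read as a decision, and the unseen SAP may already stratify. This objection stands against any claim of an error in the analysis. What remains is that the article describes the test, its diagnostics and its fallback in some detail, and someone following that text alone would run an unstratified analysis.

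A reader might also infer that the primary result would be invalid or badly underpowered. It would not. The type I error is not inflated, the unadjusted HR is a legitimate marginal estimate, and the larger power losses rest on assumed risk hazard ratios of 2.5 to 3 for which the article gives no figure.

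Finally, a reader might conclude that men aged 65 cannot be allocated. Randomisation is web-based and the trial is already recruiting, so the printed boundary is most likely a typographical slip that the live system has resolved.

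**Conclusion.** The point holds as an efficiency improvement, not as a flaw in validity. Taken as written, the primary analysis does not use the strata that shaped the randomisation. Under the stated planning values, stratifying gains about 0 to 1.5 power points with weakly to moderately prognostic strata. It gains about 3 to 5 points with risk HRs of 2.5 to 3; in the strongest scenario where the HR was estimated, it moved by 0.02. With non-prognostic strata the difference is within simulation error. These sizes rest on assumed prognostic strengths, an assumed mix of strata and exponential times. In the strongly prognostic scenarios the unstratified test falls below the stated 90% power and the stratified test does not.

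The age boundary is a real but minor error in the text. It has no bearing on the power figures and matters mainly because the analysis strata must be defined.

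**What to change.** State that the primary test is a two-sided log-rank test stratified by PCa risk (low, intermediate) and age group, with the HR from a Cox model stratified by, or adjusted for, the same two factors, and with the unstratified result as a sensitivity analysis. If the SAP already says this, confirming it is enough.

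Correct the age strata in Randomisation and population to show which group holds men aged 65, taken from the live randomisation system, and use the same definition in the analysis.

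The cost is one or two sentences. No new data and no change to the sample size are needed. The change should be made before outcomes by arm are seen.

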## Methods and analysis

### Design

Finasteride in Active Surveillance for men with low and intermediate-risk prostate cancer (FINESSE) is a randomised, prospective, non-blinded, open-label, parallel group, phase 3 trial. Men will be randomised 1:1 to receive AS plus finasteride (5 mg) for 2 years or AS alone.

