### Finasteride plus AS

Men randomised to the intervention group will receive finasteride (oral 5 mg) to be taken once a day for 2 years, in addition to AS (as above). Participants will be prescribed finasteride on a 3 monthly basis and this will be dispensed from their recruiting hospital pharmacy. Compliance will be measured using pill counts and patient questionnaires.

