## Study aims

To understand whether the addition of finasteride to AS increases adherence in men with low/intermediate-risk PCa.To understand the tolerability and compliance with finasteride within an AS regimen.To understand whether the addition of finasteride to AS reduces disease progression in these men.

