### Procedure(s) to account for missing or spurious data

We anticipate that the dropout level will be low. For the main endpoint of progression from AS participants who withdraw from the trial or who are lost to follow-up will be censored at the last attended visit or the time of notification of withdrawal.

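### Finasteride tolerability is to be analysed in every man randomised to the drug, dosed or not, which slightly understates side-effect rates if some never start

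*Protocol article*

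**What the plan says.** The Participant population section of the protocol article names a separate population for each analysis. The main endpoint uses all randomised men by intention to treat, and the quality-of-life analysis uses men who complete the questionnaires. For tolerability the rule is: "Tolerability of finasteride analysis will be performed on all participants randomised to finasteride". Nothing in that sentence depends on having taken the drug, and no other section defines a safety or dosed set.

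The analysis serves the second of the Study aims: "To understand the tolerability and compliance with finasteride within an AS regimen".

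Under Finasteride plus AS, men in the intervention arm receive "finasteride (oral 5 mg) to be taken once a day for 2 years". The drug is prescribed every three months and dispensed by the recruiting hospital's pharmacy. The same section adds: "Compliance will be measured using pill counts and patient questionnaires". The trial is open label, so each man knows his allocation before his first supply.

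**The concern.** An all-randomised population is the right default for comparing arms, because it preserves the randomisation. The tolerability sentence concerns the finasteride arm only and names no comparator, so there is no randomised comparison for it to protect. It describes what happens to men given a drug.

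A man who is randomised, learns his allocation and never takes a tablet cannot have a side effect of finasteride. He still counts in the denominator, where he looks the same as a man who took the drug without trouble. For a harm, the resulting error is in the reassuring direction. Never starting is useful information, but it bears on compliance and does not show that the drug was tolerated.

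**Working it through.** The protocol states no figure for tolerability, so there is none to reproduce. The only planned number needed is the size of the finasteride arm.

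**Inputs**

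- Arm size: 550 men allocated 1:1 (Design; Sample size), so 550/2 = 275.
- u, the share never dosed: not given. The nearest statement is "We anticipate that the dropout level will be low", which concerns dropout from the trial and carries no number. Assumed 2%, 5% and 10%.
- p, the side-effect rate in dosed men: not given. Assumed 10%, with 5% to 20% as a range.
- b, the rate of the same event in undosed men: not given. Taken first as zero. The section on usual care allows that control men may have symptoms such as erectile dysfunction unrelated to the drug, so b is above zero for some events.

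**Formula**

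Events in the arm = 275(1-u)p + 275*u*b. Dividing by 275:

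- reported rate = p(1-u) + b*u
- understatement = p - [p(1-u) + b*u] = u(p - b)

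**Results for p = 10%, b = 0**

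| u (assumed) | Men never dosed | Reported rate | Shift |
|---|---|---|---|
| 2% | 275 × 0.02 = 5.5 | 0.10 × 0.98 = 9.8% | 0.2 points |
| 5% | 275 × 0.05 = 13.75 | 0.10 × 0.95 = 9.5% | 0.5 points |
| 10% | 275 × 0.10 = 27.5 | 0.10 × 0.90 = 9.0% | 1.0 point |

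Over a wider grid with b = 0, the shift runs from 0.01 × 5% = 0.05 points (u = 1%, p = 5%) to 0.10 × 20% = 2.0 points (u = 10%, p = 20%).

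**Effect of a background rate**

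With p = 10% and an illustrative b = 5%, the shift is u × 5%. That is 0.1, 0.25 and 0.5 points for u of 2%, 5% and 10%, half the values in the table.

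**Scale against sampling error**

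For a 10% rate in 275 men, the 95% half-width is 1.96 × √(0.10 × 0.90/275) = 1.96 × 0.0181 = 0.035, or about 3.5 points. Every shift in the table is smaller than this.

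**Dependence on the measure**

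Suppose tolerability were the proportion not taking the drug, with never-starters counted as failures. That corresponds to b = 1 in the formula. The understatement u(p - 1) is then negative, so the reported rate is higher than in dosed men. The downward direction therefore holds for side-effect rates but not for every possible measure.

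**The case against.** The strongest reply is that the effect is small and its cause is assumed. Eligibility excludes men unwilling to follow the trial procedures, men with known intolerance of finasteride and men with contraindications to it, so few may fail to start. The plausible shift lies within sampling error, and a background rate shrinks it further. This stands, and it limits the point to a minor one.

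A second reply is that the aim joins tolerability with compliance. For that joint question, all men allocated to the drug are a reasonable population, since refusing to start is itself informative. This stands in part. It is a reason to report never-starters and keep the all-randomised figure, but not to count undosed men as free of side effects.

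A third reply is that analysis sets belong in the statistical analysis plan. That would answer a silence, but here the protocol states the population. An analysis plan that follows the sentence inherits it.

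A reader might also infer something larger. Treatment is planned for 2 years and active follow-up for 3 to 5 years, so side-effect rates might be spread over long periods off the drug and look much lower than they are. The article does not support this. It states who is analysed, but neither the time window nor the measure, and nowhere plans a rate per person-year over all follow-up. Table 2 separates a treatment phase from a follow-up phase. The event window is the kind of detail that an article leaves to the full protocol or analysis plan.

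**Conclusion.** The point holds as a minor one. The stated population includes men who never take finasteride. For any side effect commoner on the drug than off it, the reported rate then falls short of the rate in dosed men by u(p - b). With an assumed 2% to 10% never dosed and no background rate, a true 10% is reported as 9.8% to 9.0%.

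The never-dosed share, the side-effect rate and the background rate are all assumptions, because the protocol gives none of them. If every man starts, there is no bias. If tolerability is defined by stopping or not taking the drug, the direction may reverse. The intention-to-treat analysis of the primary endpoint is unaffected.

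**What to change.** Replace the tolerability sentence with wording such as: *Side effects of finasteride will be summarised in participants randomised to finasteride who took at least one dose, as identified from dispensing and pill-count records. The number who never started will be reported as a compliance result. The same summary in all participants randomised to finasteride will be given in support.*

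Events should not stop being counted at the last dose. A man may stop because of a side effect that is recorded only afterwards, and a cut-off there would bring back the understatement.

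The cost is one sentence, and the article already plans dispensing and pill counts. It does not say that first-dose dates are recorded, so the analysis plan should state how to classify a man who was dispensed tablets but has no pill count. The drawback is that the dosed set is slightly smaller and is not a randomised set, so it serves description only.
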